#### Physical functioning

The Short Physical Performance Battery (SPPB) (Guralnik et al., 1994) assesses lower-extremity function via balance, gait speed, and sit-to-stand performance. Balances will be tested across three progressively challenging stances (parallel (0–1 point), semi-tandem (0–1 point), and tandem stand (0–2 points); balance sum 0–4 points). To get into the specified position, participants will be allowed to hold on to an aid; however, aids are not allowed during the measurement. Gait speed will be recorded over 4 m at a comfortable pace, with an aid being used if necessary (0–4 points). Leg strength will be measured by the time taken to complete five chair rises (0–4 points). Individual scores will be summed up to a total from 0 (low mobility/functionality) to 12 points (full mobility/functionality). A change of ∼1.0–1.3 points is considered clinically meaningful (Guralnik et al., 1994).

#### Activities of daily living

*Activities of daily living (reported by others).* The Barthel Index evaluates basic activities of daily living (ADL) independence. Ten items will yield a 0–100 score reflecting dependency (Mahoney and Barthel, 1965). The items of the Barthel Index will be completed by the nursing staff.

*Activities of daily living (self-report).* The Nuernberg-Ageing-Everyday-Life Test *(NAA)* assesses daily living tasks. Seventeen NAA items relevant to nursing-home ADLs will be used (Oswald and Fleischmann, 1999). The items are scored by 1 “often” to 3 “never”. The total score ranges between 17–51 points; ≤32 points (63.3%) denotes independence.

*Life Space mobility*. The Nursing Home Life-Space Diameter (NHLSD; Tinietti and Ginter, 1990) quantifies residents’ movement across four facility zones. It tracks mobility changes and intervention effects, and it has shown acceptable inter- and intra-rater reliability. The four zones are: the resident’s private room (zone 1), the ward in which they reside (zone 2), the rest of the facility (zone 3), and the area outside the facility (zone 4). Zone-visit frequencies 0 (never) to 5 (more than three times a day) are weighted by zone level and doubled for unassisted movement (Tinetti and Ginter, 1990).

#### Cognition

*Global cognition.* The Montreal Cognitive Assessment (MoCA) is a brief 30-point screening tool for mild cognitive impairment and early stages of Alzheimer’s disease. It evaluates key domains including memory, executive function, attention, language, and orientation (Wong et al., 2018). Scores ≤25 indicate possible mild impairment; higher scores are considered normal (Nasreddine et al., 2005).

*Cognitive performance while performing single and dual tasks*. Cognitive performance will be assessed via an auditory task in which residents judge six landmarks as ‘inside’ or ‘outside’ the facility. Pre-standardized audio files (selection procedure via MATLAB R2022a, recording using the Audacity^®^ program version 3.4.1) will present the landmark in randomized order for 15–18 s. Responses (‘yes’/‘no’) will be recorded across three randomized landmark distributions to avoid bias (3 inside: 3 outside, 2 inside: 4 outside, and 1 inside: 5 outside). An initial practice will ensure audibility and comprehension. The task will be performed alone and concurrently with walking (8.5 m of walking) and posture tasks (15 s of standing still); correct responses and motor metrics will be analyzed as mentioned above.

*Spatial orientation.* Spatial orientation will be measured via a 12-item landmark recognition (LMR) test (DeIpolyi et al., 2007; Wollesen et al., 2020a). Participants must identify the four genuine facility landmarks among 12 images representing all life space zones (Jansen et al., 2017). Additionally, four “fake” images will depict similar locations elsewhere. The order of the 12 pictures will be randomly generated using MATLAB (MATLAB R2022a). Scores will be reflected in correct identifications (+1 point), unsure (0 points), and false alarms (−1 point). Total scores range from −12 to 12 points; higher scores indicate better orientation.

#### Health behavior

*Subjective age*. Participants’ subjectively perceived age will be compared to their actual current age to assess their image of age and their perceived age norms. In response to the question “How old do you feel?“, residents will answer with their perceived age.

*Subjective health*. Participants’ health behavior will be assessed with one item from the Health Survey SF12 (Ware et al., 1998). Participants will be asked to rate their general health on a 5-point Likert scale ranging from excellent to poor.

*Concerns about falls*. The Short-FES-I (Hauer et al., 2011) measures fall-related concern across daily tasks. Three non-applicable items will be omitted (items 1, 3, and 13). Each remaining question will be rated from 1 = “not at all concerned” to 4 = “very concerned.”

*Physical self-concept*. To capture residents’ physical self-concept we will use an adapted scale of the Physical Self-Concept Scale (PSC scale) by Stiller et al. (2004). We will focus on three two-item subscales (endurance, strength, and coordination), rated 1 (“disagree”) to 4 (“agree”). Mean scores will be computed for each subscale.

#### Psychological well-being and emotions

*Depression.* The Depression in Age Scale (DIA-S) screens depression in geriatric patients (Heidenblut and Zank, 2010). 10 yes/no items will assess depressive symptoms over the past 14 days. If statements 1–2, 4-6, and 8-9 are answered affirmatively and statements 3, 7, and 10 are answered negatively, all 10 depressive symptoms are confirmed. Scores ≥4 indicate probable depression; scores ≤3 are inconclusive.

*Loneliness*. Loneliness is assessed by a single Center for Epidemiological Studies Depression Scale (CES-D) item (Radloff, 1977). Residents will be asked to answer the question “Have you felt lonely in the last week?” with one of the four possible answers: “rarely or not at all (<1 day)”, “sometimes (1–2 days)”, “often (3–4 days)”, “most of the time to all of the time (5–7 days).”

*Health-related quality of life.* The European Quality of Life 5 Dimensions 3 Level Version (EQ-5D-3L) assesses health-related quality of life across five dimensions: mobility, self-care, usual activities, pain/discomfort, and anxiety/depression. Levels range from 1 (‘no problems’) to 3 (‘extreme problems’) per dimension (Brooks, 1996). A five-digit profile (e.g., 12,211) will be generated and converted into a utility score. EQ-5D-3L profiles will be converted to utility values using the German values of the European Value Study (EVS) (Greiner et al., 2005). Utilities range from 1.00 (11,111; perfect health state) to −0.36 (33,333; worst health state).

*Quality of life.* The World Health Organization’s Quality of Life (WHOQOL) assessment defines quality of life as individual’s self-related life satisfaction (WHO, 1998). A single item (“How would you describe your quality of life?”) will be rated on a 1 (‘very bad’) to 5 (‘very good’) scale.

#### Intention to be physically active and stage of change

Participants’ intention to engage in physical activity PA and their subjective status of physical activity will be assessed via two questions. Intention will be rated on a 1 to 7 agreement scale. Stage of activity (≥2.5 h/week) will be classified into five intention/adoption categories (Lippke et al., 2009).

## Interventions

We are following a participatory approach to developing and conducting environmental interventions in nursing homes. Therefore, 1 month before t1 in each participating nursing home, a workshop was conducted with representatives from all status groups. The goal was to develop a participatory strategy to integrate more PA-supporting structures into the residents’ living spaces. During the workshop, the life space mobility model by Jansen and colleagues was explained (Jansen et al., 2017). Based on that model, we determined the actual status and the desired status for the most frequently visited places in the nursing home. The results were compared to identify potential mismatches. Workshop members were then asked to identify resources, wishes, and problems to eliminate barriers and stimulate motivation for residents to leave zones 1 and 2 more often and be more physically active. Based on the workshop results, the research team developed suggestions for PA-promoting changes in the nursing home and its environment. These suggestions were reviewed by the nursing homes’ stakeholders, and suggestions for changes were incorporated before implementing the interventions (Conger and Kanungo, 1988; Cornwall and Jewkes, 1995; Jansen et al., 2017). All interventions follow the same general framework and aim to increase physical activity and physical functioning. Across all nursing homes and their residents, the interventions are tailored to the specific needs and spatial structures. This participatory process is supported by all stakeholders and adapted to the individual needs of the facilities.

A follow-up workshop will be held at each nursing home around t3 to evaluate the effectiveness of the interventions and discuss the implementation of sustainable PA promotion. An overview about all interventions is given in Table 2.

**TABLE 2 T2:** Description of the four interventions.

Intervention	Components	Week 1–4	Week 5–8	Week 9–12	Week 12–16
**Physical exercise intervention (I1, I2)**	Mobilization and warm-up (5–10 min.)	Week 1–16 • Range of motion exercise for the wrists, hips, shoulders, wrists, knees, and ankles			
	Coordination, balance, and cognitive exercises (10 min.)	Week 1–16 (with weekly progression) • Standing balance, bodyweight shifting • Simple cognitive tasks • Coordinative exercises with small equipment and everyday materials (e.g., balls, scarves) • Spatial orientation exercises, e.g., pointing to cardinal directions, assigning rooms of the facility to a map • Orientation puzzle			
	Gait training (18–20 min.)	•75–90 m • Direction pointing task	•105–120 m • Direction pointing task	•135–150 m • Direction pointing task	•165–180 m • Direction pointing task
	Muscle strengthening exercises (10 min.)	• Chair rises • Upper body and trunk exercises with additional materials and weights • Functional lower-limb exercises	cf. Week 1–4 • Individual progression of number of repetitions		
	Cool down (5–10 min.)	Week 1–16 • Stretching • Relaxation exercises			
**Guided environmental intervention (I1, I3)**	Indoor (Life-space 2–3)	Week 1–16 • Trim paths through the facility • Movement posters focusing on mobilization, strengthening, and balance • Seated bicycles and other exercise equipment • Information brochure on trim path • Before implementation: 20-minute guided training session for nursing staff • Guided group activities offered 2/week by a project worker and opportunity to be performed independently			
	Outdoor (Life-space 4)	-	-	Week 9–16 • Booklet with 4 outdoor routes (500 m to 1,500 m) • Barrier-free • Written descriptions, photos, and map • Should be walked independently • Guided group walks offered 2/week	
**Non-guided environmental intervention (I4)**	Indoor (Life-space 2–3)	Week 1–16 • Trim paths through the facility • Movement posters focusing on mobilization, strengthening, and balance • Seated bicycles and other exercise equipment • Information brochure on trim path • Before implementation: 20-minute guided training session for nursing staff • Should be performed independently			
	Outdoor (Life-space 4)	-	-	Week 9–16 • Booklet with 4 outdoor routes (500 m to 1,500 m) • Barrier-free • Written descriptions, photos, and map • Should be walked independently	

Note: I1 Intervention 1, Physical activity culture (combination of physical exercise intervention and guided environmental intervention); I2 Intervention 2, Physical exercise intervention; I3 Intervention 3, Guided Environmental intervention; I4 Intervention 4, Non-guided environmental intervention.

### Combined physical exercise and guided environmental intervention (physical activity-promoting culture)

During the physical activity-promoting culture intervention, exercise and guided environmental interventions as described below will be synergistically implemented in a participatory process. Additional information can be found in Table 2.

### Physical exercise intervention

The exercise program intervention will consist of 32 sessions of 45–60 min each. The intervention will be conducted over 16 weeks and offered twice per week. Group sizes will be up to 10 participants per training session. One certified exercise scientist or physiotherapist will conduct every session and be supported by an assistant. The programme was developed following the guidelines of the International Association of Gerontology and Geriatrics (IAGG), and the exercise intervention is based on the *PROfit orientation* program by Wollesen et al. (2020b). This programme aims to improve PA, LSM, and spatial orientation. The program will be modified for an intervention period of 16 weeks (formerly 12 weeks) and adapted to the nursing home settings. Further, the program will be continuously adapted to residents’ abilities and needs. Exercises that do not work well will be replaced by more appropriate and acceptable exercises, while the target of the replaced exercises should remain the same. To increase motivation and participation, incentives such as stamp cards and monthly awards certificates for the most frequent participation will be introduced. Further details are provided in Table 2.

### Guided environmental intervention

The environmental intervention will focus on material-structural environmental changes, as well as creating supply and availability structures for PA (Franzkowiask, 2022). The overall aim is to improve PA both inside and outside the facility. Therefore, engaging and stimulating exercise stations will be created at different locations in the care facility that can be independently used by residents. These stations will be developed in a participatory manner and designed under consideration of exercise principles. Examples of exercise stations are exercise posters or exercise stations with equipment like balls or walking routes. Following the principle of nudging, these posters/exercise stations will be placed at multiple locations in the nursing home so that residents are invited to be active in different life spaces of the nursing home (Eichhorn, 2019). Further, they might feel invited to expand their LSM by visiting exercise stations in life space zones 2–3 (Jansen et al., 2017). As a further motivational factor, exercise stations can be integrated into paths with different levels of difficulty (just zone 2 up to zones 2 + 3). To integrate zone 4 into the environmental intervention, a brochure containing a map, text, and pictures of different outdoor routes will be developed to help residents find their way around the area outside the nursing home. The intervention will run for 16 weeks, and it will be promoted by a sports scientist two to four times a week for 45–60 min each session. The sports scientist will explain the exercise stations to residents, supervise their use, and provide guidance on correcting motor movements, offering motivation, and adapting exercises according to the residents’ needs and abilities. More information on the guided environmental intervention is presented in Table 2.

### Non-guided environmental intervention

The non-guided environmental intervention will use the same materials as the guided environmental interventions. However, this intervention will not be supervised or guided, so participants must engage independently, with the assistance of nursing home employees or relatives. This non-guided environmental intervention also serves as the follow-up condition between t3 and t4 (see Table 2).

## Data management and analysis

### Data management

Electronic data will be stored on a university server that is backed up on a hard drive using the SPSS software. Only the leading project staff will have access to the server. Data that is originally in paper format and has been digitized will be stored separately in a locked cabinet. The data will be stored and identified only by pseudonymized ID codes. The code list with the participants’ names and combined ID codes will only be available to the leading project staff and will be stored separately from the data in a locked cabinet. Double-checking and plausibility checks will be performed to verify data quality.

### Statistical analysis

The descriptive statistics will be presented as either group mean values and standard deviations/errors or medians and interquartile ranges, depending on the distribution of the outcome measures. The intervention effect for the primary outcomes (Number of Steps and SPPB) will be analyzed separately using a 4 (between group: PA-promoting culture intervention, guided environmental intervention, non-guided environmental intervention, or exercise intervention) × 2 (within test time point: t1:t2, and t2:t3) linear mixed model, where participants can be nested within nursing homes and be calculated as a random effect. The Follow-Up effects will be analyzed additionally using a 4 (between group: all interventions) x 3 (within test timepoint: t1/t2 – t2/t3 – t4). If baseline differences are found, the baseline assessment values, as well as age and sex discrepancies, will be included as covariates in the statistical model. In cases of statistically significant interaction effects, Bonferroni-adjusted *post hoc* tests (such as t-tests or Wilcoxon tests) will be employed to identify significant differences between groups from baseline to post-allocation testing. The data will be pre-processed and analysed using SPSS.

The effect size will be determined using Cohen’s f, which indicates the magnitude of treatment effectiveness and helps assess whether a statistically significant difference is practically significant (Cohen and Ebl, 1988). Cohen’s f values are classified as small (0 ≤ f ≤ 0.24), medium (0.25 ≤ f ≤ 0.39), or large (f ≥ 0.40) (Grissom and Kim, 2011). For *post hoc* analysis, Cohen’s d effect size will be calculated. Additionally, PSdep scores (probability of superiority for dependent samples) will be calculated as an estimate of effect size in non-parametric *post hoc* tests. The significance level will be set at p < 0.05. An intention-to-treat analysis will be conducted, considering all participants in the groups to which they were randomly assigned, regardless of whether they received or adhered to the assigned intervention. We will control participation in the interventions to analyze the effect of the intervention in more detail. Multiple imputations will be used to handle missing data, assuming that the missingness is random. If more than 40% of participants are lost to outcome assessment or demonstrate insufficient participation in training sessions, an additional per-protocol analysis will be conducted.

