#### Eligibility criteria

Inclusion criteria are: (i) voluntary participation, (ii) ability to participate in group training, (iii) minimum age of 60 years, (iv) ability to understand and implement instructions given by a trainer, and (v) ability to sit freely in a (wheel)chair. No other criteria are applied. If a study participant no longer fulfills the inclusion criteria due to a natural, age-related deterioration in general condition, they will be excluded from study participation (but they will be welcome to continue participating in the interventions voluntarily).

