### Primary outcomes

#### Physical activity (PA)

The *Fitbit Zip* (Fitbit, San Francisco, United States) device will be used to objectively track PA, and its 6-month battery life supports prolonged use. The Fitbit Zip has been validated for use in different age groups and conditions (Tully et al., 2014; Sharp et al., 2017; Streber et al., 2017), and it has been shown to deliver data that is considerably more accurate than subjective measures and close to that of the “gold standard” ActiGraph (Meyer et al., 2019). The Fitbit will be attached to participants’ clothes and will record their steps taken and distance traveled, which can be viewed on the Fitbit’s display. Participants will be instructed to wear the Fitbit Zip as often as possible throughout the project duration (52 weeks), immediately after waking up, and to remove it before going to bed. The data will be synced weekly; malfunctioning devices will be replaced (Tully et al., 2014; Sharp et al., 2017; Streber et al., 2017). To analyze steps per day, hours with at least one step will be identified as wearing hours (Meyer et al., 2016). Days with less than 6 h (identified as less than 6 h with at least one step) or not fulfilling the “three-a-day” criterion (using the tracker at least once in the morning, once around noon, and once in the afternoon, identified as at least one step having been registered) will be excluded from PA calculations. These days will be classified as non-wearing days, according to the heuristic of Meyer and colleagues (Meyer et al., 2017). Sedentary minutes will be defined as periods of at least 20 min with three or fewer steps per minute (Meyer et al., 2019). To calculate sedentary time and the *longest zero* time, we will exclude data from days with less than 6 hours of wearing. To express sedentary minutes as a percentage of total waking time, waking time will be defined as a 12-h period (Alessi et al., 2005). This definition of waking time is necessary because it is difficult to distinguish between non-wearing time and sedentary time (Meyer et al., 2017). Usage behavior will be quantified as the proportion of days worn.

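### Pairwise claims are opened by a linear mixed model but decided by stand-alone t-tests or Wilcoxon tests, which drop the model's home effect and covariates and may test a different hypothesis

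*Protocol article*

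**What the plan says.** The Statistical analysis section states: "The intervention effect for the primary outcomes (Number of Steps and SPPB) will be analyzed separately". Each of the two outcomes gets its own model: four interventions by two test intervals, described as "within test time point: t1:t2, and t2:t3) linear mixed model". Participants can be nested in homes as a random effect. Baseline values, age and sex enter as covariates if baseline differences appear.

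A significant interaction opens a second step, Bonferroni-adjusted post hoc tests "such as t-tests or Wilcoxon tests) will be employed to identify significant differences between groups". Cohen's d is the effect size for these, and a probability of superiority for dependent samples "will be calculated as an estimate of effect size in non-parametric" follow-up tests.

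On distribution, the section makes descriptive summaries conditional: means, or "medians and interquartile ranges, depending on the distribution of the outcome measures". The Wilcoxon option gives the post hoc step similar freedom. Nothing comparable is stated for the model. The section adds "The data will be pre-processed and analysed using SPSS", without saying what the pre-processing is.

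**The concern.** The study hypotheses are pairwise: the combined intervention against each component, and each component against the non-guided arm. The post hoc tests therefore carry the trial's conclusions, and the model only decides whether they are run. A method chosen to respect homes and repeated periods is replaced, at the deciding step, by tests that respect neither.

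Two things are at stake. If changes cluster by home, the pairwise p-values are too small. And if the follow-up is a rank test, the pairwise result does not answer the question that opened it. A few residents with large step gains could open the gate on mean change while the rank test finds nothing. A consistent shift in ranks could equally fail the gate and never be tested.

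**Working it through.** **1. The two steps side by side.**

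| | Interaction test | Post hoc test |
|---|---|---|
| Method | Linear mixed model | t-test or Wilcoxon |
| Hypothesis | Equal mean change across arms | Equal means, or equal ranks if Wilcoxon |
| Home random effect | Can be included | None |
| Covariates | If baseline differs | None |
| Crossover structure | Can be modelled | Independent or paired, not both |

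**2. Neither simple test fits the design.** Under Trial design, each intervention is paired once with each of the other three, giving six homes. Arm A therefore runs in homes AB, AC and AD, and arm B in AB, BC and BD. Any two arms share one home of their three. With 10 to 20 residents per home (Sample size estimate), take the midpoint of 15. Each arm then has 3 × 15 = 45 participant-periods, and 15 of those residents appear in both arms. An independent-samples test treats these 15 as different people. A paired test between arms can use only those 15 of 45. A paired pre/post test within an arm compares no arms at all. The effect size for dependent samples leaves open which is meant.

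**3. Size of the error if clustering is ignored.** Inputs: m = 15 residents per home, three homes per arm, and an intraclass correlation ρ of change within a home-period. The value of ρ is assumed. For simplicity the two arms are treated as having separate homes.

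Variance inflation: D = 1 + (m − 1)ρ. True two-sided error of a test using critical value z: 2[1 − Φ(z/√D)].

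| ρ | D | Nominal 5% (z = 1.960) | Nominal 0.83% (z = 2.638) |
|---|---|---|---|
| 0.02 | 1 + 14 × 0.02 = 1.28 | 8.3% | 2.0% |
| 0.05 | 1 + 14 × 0.05 = 1.70 | 13.3% | 4.3% |
| 0.10 | 1 + 14 × 0.10 = 2.40 | 20.6% | 8.9% |

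The last column assumes Bonferroni over all 4 × 3/2 = 6 pairs: 0.05/6 = 0.0083. Simulation of the same layout agrees, with about 8% at ρ = 0.02 and 20 to 22% at ρ = 0.10 for the nominal 5% test. Over the protocol's range of home sizes, the nominal 5% column runs from 7.1% (m = 10, ρ = 0.02, D = 1.18) to 25.0% (m = 20, ρ = 0.10, D = 2.90).

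**4. Does the scale of the step count matter?** The protocol gives no SD, median or shape for steps, so every figure here is conditional. All are one-way F tests on change with 22 per arm and no clustering.

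- Log-normal steps, proportional effects set to 80% power on the log scale, α = 0.025. Power raw vs log: 82 vs 79% (CV 0.31), 78 vs 80% (CV 0.53), 71 vs 79% (CV 0.80), 59 vs 80% (CV 1.12).
- Gamma steps, also right-skewed, gains of +40/+20/+20/0%, α = 0.05. Power raw vs log: 60 vs 49% (CV 0.5), 31 vs 25% (CV 0.7).
- Under log-normal steps the type I error was not inflated on the raw scale: 1.5 to 2.5% against a nominal 2.5%.

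The ranking reverses when only the assumed shape and effect setting change.

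**The case against.** The post hoc tests run only after a significant interaction and are Bonferroni-adjusted, so the gate protects against false claims when no arm differs. That is true, but only for that case. Once one arm truly differs, the gate opens rightly and the other pairs are left to the unclustered test.

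A second objection is that analysing change removes a home's stable level. This also stands, and it is why the calculation uses the correlation of changes. That correlation could be near zero. However, the interventions are tailored to each home and delivered in groups, so home-specific change is plausible.

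Third, the wording only gives examples of tests, and a fuller analysis plan may be more precise. But both examples are stand-alone tests, so this is a stated rule and not mere silence.

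A reader might go further and infer that the plan expects skewed steps, that raw counts in a linear model lose power, and that log steps should be primary. Mixed mobility does make right skew plausible: the entry criterion is only "ability to sit freely in a (wheel)chair". But the wording on distribution is conditional, the valid-day rule trims the low end, and no spread or shape is given. A transformation may also sit in an analysis plan that is not shown. The log scale would change the target from mean steps to a ratio.

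**Conclusion.** The point holds for the pairwise step. The plan gates on one method and decides with another that omits the home effect and covariates, cannot represent the crossover, and in the Wilcoxon case tests a different hypothesis. This mismatch follows from the text alone.

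The size of the error does not. The 8% to 21% for a nominal 5% t-test rests on an assumed correlation of change of 0.02 to 0.10, 15 residents per home and separate homes per arm. It describes a single comparison and ignores the protection of the gate.

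The stronger claim about step counts is not supported. Which scale has more power depends on an unknown CV, an unknown shape and whether gains are proportional or constant. The simulations give no sign that the raw scale inflates the type I error of the interaction test. Steps per day warrants a prespecified check, not a change of primary scale.

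**What to change.** Replace the sentence on post hoc tests with a rule that the Bonferroni-adjusted pairwise contrasts, with 95% confidence intervals, are estimated from the same fitted mixed model, and state how many contrasts are adjusted for. The model's random part should cover home-specific change in a period as well as home level, because a home intercept alone largely cancels out of change and would leave the problem in step 3 of the working.

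For steps per day, add a prespecified residual check and a log-scale analysis as a sensitivity analysis, reported as ratios. The log is defined for every counted day, since days "identified as less than 6 h with at least one step" are excluded and each remaining day has at least six steps. If that rule changes so that zeros can occur, use a log-link model.

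The cost is two or three sentences, with no new data and no change to the primary outcome. Intervals may be wider than those from stand-alone tests, which reflects having only six homes.
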